## 7.9 LOGISTICS

Recognising that it is critical to ensure collaboration across teams and departments from the start, we will ensure all PIs, cath lab nurse managers, and any staff to whom patients present (e.g. A&E), are invited to attend initial local/regional meetings. The senior applicants have been involved in studies where engagement of all stake-holders has been essential (e.g. STREAM trial paramedics). We expect all eligible patients to be approached in each of the sites. The inclusion criteria are broad and the exclusion criteria limited, and mostly to those patients that would require emergent treatment based on haemodynamic instability. Taking account of patient's willingness to be involved in any study and available resources, we would expect to include >75% of patients seen. This strategy will help to ensure that all eligible patients are considered for the trial. An important measure will be the time between randomisation to immediate angiography with proposed follow-on revascularisation (Group A) and the actual time of intervention. Our focus will be on supporting staff (PIs, research nurses, cath lab teams) and engaging them in the trial ethos. We will include large sites with very active ACS programmes and with the cath lab and the A&E/CDU/MAU on the same site to allow for the early group (A) to suffer little delay. Depending on recruitment we expect that extension of the trial to later in the working day and to beyond the working week to be considered as the trial progresses.

Review of ongoing studies that might compete for the same population or whose results might affect recruitment has been undertaken: A search on [clinicaltrials.gov](https://clinicaltrials.gov) has shown no ongoing studies that would compete for recruitment of N-STEMI ACS patients to RAPIDNSTEMI. The BHF study (Senior RITA) may pose competition for sites and patients but we have recruited 25 confirmed sites participating in RAPIDNSTEMI.

The DANCE pilot study aimed to recruit 200 patients from 4 sites in London to assess the efficacy of transporting N-STEMI ACS patients to regional PCI-capable sites for invasive management. ICON-1 study is recruiting ACS patients over 65yrs only within a single centre (n=300).

GLOBAL-LEADERS is an "all comers" study evaluating use of 1 vs 2 antiplatelet agents following PCI; it is not exclusively recruiting N-STEMI patients. None of these studies address the primary question of timing of intervention in the acute phase of N-STEMI and hence the results of these studies would not affect recruitment into RAPIDNSTEMI. Given the UK-wide PCI rates for N-STEMI ACS (approx. 36,000 in 2014) and our broad inclusion criteria, we consider recruitment to RAPIDNSTEMI will be completed within time. Based on UK-wide data from Myocardial Ischaemia National Audit Project (MINAP) and British Cardiovascular Intervention Society BCIS we feel that the required recruitment rate of 4 patients per month per centre will be the minimal requirement needed and should be achievable.

Estimated Consent Rate: With 25 sites recruiting over a period of 24 months, the minimum consent rate from would be 4 patients per month per centre. We have polled and have data to suggest UK Interventionist support for this study. At a minimum of 4 patients per month, 25 sites over 24 months will recruit 2400 patients.

RAPID-NSTEMI

[figure not shown]

TABLE 2: SUMMARY OF BASELINE, RANDOMISATION AND FOLLOW-UP PROCEDURES

| Procedure                               | Visit window | On admission | 24 hours post admission | Pre-angiography (STANDARD arm Group B only) | Within 24hrs post angiography | Pre-discharge | Day 7 +/- 3 days | 30-days (Telephone) +/- 1 week | 6months (Telephone) +/- 2weeks | 12months Clinic visit/ telephone +/- 4weeks |
|-----------------------------------------|--------------|--------------|-------------------------|---------------------------------------------|-------------------------------|---------------|------------------|--------------------------------|--------------------------------|---------------------------------------------|
| Eligibility assessment                  |              | •            |                         |                                             |                               |               |                  |                                |                                |                                             |
| Demographics                            |              | •            |                         |                                             |                               |               |                  |                                |                                |                                             |
| ECG                                     |              | •            | •                       | •                                           | •                             |               |                  |                                |                                | •                                           |
| Hs-Troponin                 |              | •            |                         | •                                           | •                             |               |                  |                                |                                |                                             |
| FBC                                     |              | •            | •                       | •                                           | •                             |               |                  |                                |                                |                                             |
| U&E                                     |              | •            | •                       | •                                           | •                             |               |                  |                                |                                |                                             |
| Blood sugar                             |              | •            |                         |                                             |                               |               |                  |                                |                                |                                             |
| Cholesterol                             |              | •            |                         |                                             |                               |               |                  |                                |                                |                                             |
| Medical History                         |              | •            |                         |                                             |                               |               |                  |                                |                                |                                             |
| GRACE 2.0 score                         |              | •            |                         |                                             |                               |               |                  |                                |                                |                                             |
| Assent                      |              | •            |                         |                                             |                               |               |                  |                                |                                |                                             |
| Randomisation                           |              | •            |                         |                                             |                               |               |                  |                                |                                |                                             |
| Informed written Consent    |              |              |                         |                                             |                               | •             |                  |                                |                                |                                             |
| Frailty score                           |              |              | •                       |                                             |                               |               |                  |                                |                                |                                             |
| CMR                         |              |              |                         |                                             |                               |               | •                |                                |                                |                                             |
| Biomarkers                  |              | •            |                         |                                             | •                             |               |                  |                                |                                |                                             |
| Echocardiogram                          |              |              |                         |                                             |                               | •             |                  |                                |                                | •                                           |
| EQ-5D-5L                                |              |              |                         |                                             | •                             |               |                  | •                              | •                              | •                                           |
| Seattle angina score                    |              |              |                         |                                             | •                             |               |                  | •                              | •                              | •                                           |
| Clinical Status: MACE events            |              |              |                         |                                             |                               | •             |                  | •                              | •                              | •                                           |
| Concurrent medication recording         |              | •            |                         | •                                           |                               | •             |                  | •                              | •                              | •                                           |
| Adverse Events (SAEs up to 12 month FU) |              | •            | •                       |                                             | •                             | •             | •                | •                              | •                              | •                                           |

Group A = 2 Troponins: on admission and within 24 hours post angiography  
Group B = 3 Troponins: on admission, pre angiography and within 24 hours post angiography (patients will have a Troponin measured prior to their procedure taken from the arterial sheath)  
 Or written consent, depending on local regulatory guidelines (applicable to sites in Northern Ireland/Scotland only)  
Written informed consent to be taken as soon as possible following randomisation for English and Welsh sites. Sites in Northern Ireland/Scotland may be required to take written informed consent prior to randomisation  
CMRI (Cardiac Magnetic Resonance Imaging) Limited sites participating  
Selected sites participating, samples taken at specified time points  
FBC = Full blood count  
U&E = Urea, electrolytes, creatinine, eGFR

RAPID-NSTEMI

[figure not shown]

EQ-5D-5L = EuroQol quality of life assessment

RAPID-NSTEMI[figure not shown]**7.10 IN-PATIENT MANAGEMENT GUIDELINES**

Further details of study related procedures including guidance for consent, clinical care and completing eCRFs will be provided in the study Manual of Operations which will be issued to all sites and will form the basis of site training. PCI procedures will be carried out according to current national and international guidelines and locally accepted practice. Stent implantation is according to local standards of care but drug eluting stents (excluding bioabsorbable devices) will be used in all cases unless there are clear contra-indications. Requirement for multi-vessel revascularisation to the N-IRA, will be at the operator's discretion. Prior to PCI, blood will be drawn for FBC, U&Es, according to routine clinical practice and results made available for trial purposes. All patients (except for those in 1 centre) will receive oral Ticagrelor loading dose 180mg on arrival and after diagnosis of N-STEMI ACS as per local practice, a maintenance dose of 90mg twice daily will be prescribed. The site that uses clopidogrel will load the patient with 600 mg of the drug and thereafter prescribe 75 mg per day. The use of Abciximab/Bivalirudin will be discouraged and used **only** where appropriate but this group of patients should form a minority. Such agent use will be recorded in the eCRF. Specific procedural details will be recorded. The use of oral anti-coagulant as per the patient with Atrial Fibrillation will be noted and OAC type recorded.

At 24 hours post PCI routine blood tests are repeated for Hs-Troponin-T/I, FBC and U&E as per usual clinical practice. A further Troponin will be taken in Group B patients prior to their angiography?proceed i.e. after the interim period to the to the procedure (taken from the procedural sheath).

Repeated Hs-Troponin-T/I should be taken again if there any recurrent symptoms of ischaemia. Prior to discharge a transthoracic echocardiogram will be undertaken for LV ejection fraction and regional wall motion abnormality as is standard practice. If the patient is in the CMR sub-study then Cardiac Magnetic Resonance imaging scan will also be undertaken 7+/-3 days to evaluate LV function and infarct size. Additional CMR outcomes are highlighted in the CMR substudy protocol (appendix V).

Adverse events (efficacy and safety end-points) and secondary end-points are collected pre-discharge (Appendix II). Optimal secondary prevention therapy is mandated (Appendix iv).

All medication that is prescribed should be deemed clinically appropriate for the individual patient by the local investigator. All patients will be discharged and will take dual anti-platelet therapy 12 months according to NICE guidelines for ACS. All patients will remain on aspirin (75mg) for the continuation of the study period according to local practice. Patients who require additional anticoagulation can be treated additionally with an anticoagulant (Coumadin, warfarin, novel oral anti-coagulants NOAC) according to the clinical requirements. The CHADS-2-VASC and HAS-BLED scores should be calculated to decide the necessity and risks of anticoagulation. Current ESC Guidelines should be followed.

Patients should receive baseline secondary-prevention medication, including a long-acting beta-blocker along (or heart rate-limiting calcium antagonist) with an ACE-inhibitor (or angiotensin II receptor antagonist [A2RA] if ACE-I intolerant) at maximum tolerated dose. Patients should receive high dose statins unless there is documented prior hypersensitivity

RAPID-NSTEMI[figure not shown]

or unacceptable side effects. Lipid profile will be optimized as fully as possible to reach LDL levels <2mmol/L. Patients with diabetes mellitus should be managed aggressively as per local guidelines with a period of insulin therapy to achieve good glycaemic control. Medications should be up-titrated to maximum tolerated dose within secondary prevention recommendation to meet the treatment targets, with the use of additional anti-hypertensive medications permitted. Additional anti-anginal medications, e.g. non-dihydropyridine calcium antagonists or long-acting nitrates/Nicorandil are permitted but their use is not considered a pre-requisite prior to symptom-driven invasive investigation if adequate baseline secondary prevention medication has been established. Cardiac rehabilitation should be offered to all patients including dietary advice and referral for smoking cessation therapies. Within either group, continuous clinical monitoring should be maintained along with usual clinical care. Thus, the onset of new symptoms consistent with ischaemia in haemodynamically stable patients should wherever possible be confirmed by non-invasive imaging test before considering coronary angiography.

Suggested treatment targets include:

Random total cholesterol  $\leq 4\text{mmol/l}$ , LDL  $\leq 2\text{mmol/l}$

BP  $\leq 130/80$  mmHg in all patients

HbA1C  $\leq 7\%$  in diabetic patients

### 7.11 PROCEDURES AT DISCHARGE

At discharge patients will have an ECG, the study case report form will be completed. The EQ-5D-5L and Seattle Angina Questionnaire will be completed within 24-hour post PCI in both groups.

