**7.8 INTERVENTION**

If randomised to immediate angiography (+/- intervention), the patient will be transferred to the cardiac catheterisation lab with no further avoidable delay similar to those on a STEMI pathway. At angiography the interventionist will decide, in accordance with usual criteria whether the patient should receive revascularisation (PCI or CABG) or whether they need no further management due to absence of flow limiting coronary obstruction, or whether the disease should be treated with medication alone. Routine practice including use of FFR to inform the clinician will be expected. All decisions will be documented in the eCRF. If the

RAPID-NSTEMI

[figure not shown]

appropriate intervention is PCI, then all things being equal the procedure will be completed at that sitting.  
Planned management of any non-infarct related artery (N-IRA) disease will be allowed and documented as being planned at the time of the first intervention.

If randomised to Group B the patient will be managed on an appropriate acute ward and receive subcutaneous LMWH, DAPT (Aspirin plus Ticagrelor/clopidogrel), and secondary prevention medication as per standard practice, including high dose statins. These patients will be listed for coronary angiography as per current standard care for N-STEMI patients for that hospital.  
Planned management of any N-IRA disease will be allowed and documented as being planned at the time of the first intervention.  
A screening log of potentially eligible but non-included patients with reasons, will be kept and reviewed regularly by the trial management group, screening log data will also be included in the reports to both the TSC and DSMC.

If the immediate Troponin is negative, patients will be considered to be suffering unstable angina and are NOT eligible for randomisation and will be managed according to the responsible physician standard of care for such patients. A second sample may be taken at 3 hours in line with current European guidelines, and if elevated, the participant may be randomised.

All patients will be approached as soon as possible following randomisation for formal consent to remain in the study: a patient information sheet and a consent form for signature will be given to the participant. Once written consent has been obtained participants allocated to group A will complete a quality of life baseline form (EQ-5D-5L).

A repeat Troponin will be undertaken within 24 hours after PCI.

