An additional Troponin will be taken from the standard of care group prior to their planned angiography.

Table 1: Troponin & EQ5D-5L

|                                              | ADMISSION           | FOLLOWING RANDOMISATION | PRE ANGIO ?PROCEED | Within24 HOURS POST PCI     |
|----------------------------------------------|---------------------|-------------------------|--------------------|-----------------------------|
| GROUP A
EARLY ANGIO?PROCEED               | ASSENT*
TROPONIN | CONSENT                 |                    | TROPONIN
EQ-5D-5L
SAQ |
| GROUP B
STANDARD OF CARE
ANGIO?PROCEED | ASSENT*
TROPONIN | CONSENT                 | TROPONIN           | TROPONIN
EQ-5D-5L
SAQ |

\*or written consent, depending on local regulatory guidelines (applicable to sites in Northern Ireland/Scotland only).

RAPIDNSTEMI[figure not shown]

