### **4. Statistics and power calculations**

#### **Sample size**

With the available resources we will be able to collect and analyse two samples (pre and post-angiography) from 550 patients. It is expected that approximately two-thirds of patients in our cohort will require PCI. If we recruit 550 patients, we expect approximately 367 to require PCI and 183 to not. Based on these 550 patients, 80% power and a 5% significance level, we can calculate the following for the three novel biomarkers.

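### The first EQ-5D-5L and SAQ (and the post-procedure bloods) are triggered by PCI in sections 7.8, 7.10, 7.11 and Table 1 but by angiography in Table 2, so patients without PCI are covered by one rule and not the other

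*Protocol*

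**What the plan says.** Four places use PCI as the trigger:

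- Section 7.8, repeat troponin: "A repeat Troponin will be undertaken within 24 hours after PCI".
- Table 1, troponin, EQ-5D-5L and SAQ in both groups, under the column "Within24 HOURS POST PCI".
- Section 7.10: "At 24 hours post PCI routine blood tests are repeated for Hs-Troponin-T/I, FBC and U&E as per usual clinical practice".
- Section 7.11: "The EQ-5D-5L and Seattle Angina Questionnaire will be completed within 24-hour post PCI in both groups".

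Table 2 places troponin, FBC, U&E, EQ-5D-5L and SAQ under "Within 24hrs post angiography". Its footnote 1 repeats the angiography anchor for each arm: "Group A = 2 Troponins: on admission and within 24 hours post angiography" and "Group B = 3 Troponins: on admission, pre angiography and within 24 hours post angiography".

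Two further sections name neither event. Section 7.2.2, which defines the two questionnaire outcomes, and section 8.3, which takes the EQ-5D-5L into the QALY calculation, refer only to the procedure. Section 8.3 also links that assessment to formal consent.

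Section 7.8 separately asks Group A, and only Group A, to complete an EQ-5D-5L form once written consent is given, with no condition on treatment. That form appears in neither table as an item of its own.

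**The concern.** PCI and angiography define different populations. Randomisation precedes angiography, and section 6.5 and Appendix VII expect some patients to have CABG, some to have normal coronaries and some to be treated medically. All of these have an angiogram and no PCI. For such a patient a site cannot follow Table 1 and Table 2 together. For a CABG patient, the procedure in 7.2.2 could be the angiogram or the operation.

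EQ-5D-5L and SAQ are secondary outcomes in a trial analysed by intention to treat, and section 7.4 puts all patients into the cost-effectiveness analysis. Under a PCI trigger, the first time point compares only patients whose angiogram led to PCI, a selection made after randomisation. Section 8.3 allows multiple imputation, but a site that follows the PCI wording would have no values from non-PCI patients at that time point to inform it.

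The Group A-only form adds a second problem. If it counts as the first EQ-5D-5L, Group A is covered whatever the treatment and Group B is not, so missing first utilities would differ by arm.

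**Working it through.** **The rules side by side**

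| Item | PCI trigger | Angiography trigger | Other wording |
|---|---|---|---|
| Troponin | 7.8, Table 1, 7.10 | Table 2 and footnote 1 | – |
| FBC, U&E | 7.10 only | Table 2 | Table 2 also schedules both at 24 hours after admission |
| SAQ | Table 1, 7.11 | Table 2 | 7.2.2: procedure |
| EQ-5D-5L | Table 1, 7.11 | Table 2 | 7.2.2 and 8.3: procedure; 7.8: after consent, Group A only |

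**Inputs**

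- Randomised: 2314, or 1157 per arm (section 8.1).
- CABG: about 8% (section 6.5, Appendix VII).
- Normal coronaries: a few per cent (Appendix VII). I assume 3% for illustration.
- Medically treated: expected, but no figure given (Appendix VII).
- PCI share in the biomarker sub-study (Appendix VI): "It is expected that approximately two-thirds of patients in our cohort will require PCI".

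**Reproducing the protocol's split.** 550 × 2/3 = 366.7 and 550 × 1/3 = 183.3. These match the 367 and 183 in Appendix VI.

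**Patients without PCI, out of all randomised**

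- Floor, CABG only: 2314 × 0.08 = 185.
- CABG plus the assumed 3%: 2314 × 0.11 = 255. The medically treated group comes on top and cannot be sized from the main-trial text.
- Sub-study expectation: 2314 × 1/3 = 771 (770 with the rounded split 183/550).

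This range applies to the first SAQ and the post-procedure troponin. It applies to the first EQ-5D-5L if only 7.11 and Table 1 are read. Each figure is the maximum for its assumed PCI share, reached only if every site follows the PCI wording.

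**EQ-5D-5L if the 7.8 form counts.** Only Group B patients without PCI are left out:

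- Floor: 1157 × 0.08 = 93, and 93/2314 = 4.0% of all randomised.
- With the assumed 3%: 1157 × 0.11 = 127, or 5.5%.
- Sub-study expectation: 1157 × 1/3 = 385.7 (385 with 183/550), about one sixth (16.7%) of all randomised. All are in Group B, where they are one third of the arm.

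**The case against.** The strongest reply is that PCI is loose shorthand for the procedure. Section 7.11 says both groups, Table 2 and its footnote are explicit for each arm, and section 7.10 leaves eCRF guidance to a Manual of Operations that is not shown. Sites may therefore all work to Table 2 and nothing be lost. This limits how far the loss can be predicted, but it does not remove the conflict: four places say PCI, and Table 1 is itself a schedule that sites can follow.

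Three stronger readings are tempting, and the protocol does not support them.

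- *A third of randomised patients will have no first EQ-5D-5L.* The 7.8 form covers Group A regardless of PCI, and 7.2.2 and 8.3 are ambiguous rather than tied to PCI. The one-third figure is the sub-study's expectation for its own cohort. Those patients come from the main trial at selected sites, so it is a reasonable upper figure, but the main-trial text supports only a floor of about 8%.
- *This is structural missingness far above the planned 5% drop-out.* That allowance belongs to the sample size for the binary primary outcome and has no bearing on questionnaire completion.
- *Patients without PCI have no bloods after their angiogram.* Section 7.8 names only troponin, and Table 2 schedules FBC and U&E for everyone at 24 hours after admission. With randomisation within 6 hours of admission and transfer recommended, though not mandated, within 90 minutes of that (6 + 1.5 = 7.5 hours), that sample would follow angiography for most of Group A. FBC and U&E are not listed outcomes. The troponin conflict stands, because Table 2 has no troponin at 24 hours after admission.

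**Conclusion.** The contradiction is real and should be corrected. It affects the first time point of two secondary outcomes, the first QALY utility and the timing of the post-procedure troponin. The primary outcome and the later EQ-5D-5L and SAQ assessments are untouched.

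The size depends on how many sites follow the PCI wording, which the protocol does not allow anyone to predict. If all did, the first SAQ would be missing by rule in at least about 185 patients (8%), in about 255 (11%) if normal coronaries are 3%, plus an unquantified medical group, and in up to about 771 (33%) if the sub-study's PCI share holds for the whole trial. For EQ-5D-5L the same range applies if the 7.8 form does not count. If it does, the gap is at most about 385 patients (16.7% of all randomised), but it lies wholly in Group B, which is awkward for a between-arm comparison.

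**What to change.** Use one anchor for EQ-5D-5L and SAQ: within 24 hours after index angiography, whether or not PCI or CABG follows. This is the schedule Table 2 already contains. Write it into 7.2.2, Table 1, 7.11 and 8.3, and replace the reference in 8.3 to completion alongside consent.

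Either apply the EQ-5D-5L form in 7.8 to both arms at that same time point, or remove it.

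State that a randomised patient who has no angiogram completes both questionnaires before discharge.

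Reconcile the troponin, FBC and U&E timing in 7.8, Table 1 and 7.10 with Table 2. Which timing is right is for the clinical team.

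The cost is wording changes, one eCRF trigger and a few extra questionnaires in patients without an angiogram. Patients who have an angiogram gain nothing that Table 2 does not already schedule.
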